### Participant timeline

[figure not shown]

### Sample size

Approximately 1’500 refugees reside in the initial intake facilities at the collaborating sites and could potentially participate. We estimate that approximately 30–50% will participate in the study over the years. Figure A.1 shows the power of our study with variations in sample size, effect size and predictors. It is important to note that our sample size will follow the naturalistic parallel group design of our study and thus may differ from the estimated sample size (See Fig. 3).

**Fig. 3 Fig3:**
[figure not shown]
A priori power analysis estimation based on effect sizes of 0.02 (top), 0.05 (centre) and 0.10 (bottom) for a confidence interval of 95% and a sample size per group of 0 to 1000. Calculations were done using the pwr 1.3–0 package in R [140]

### Recruitment

Social workers on site inform refugees in collaborating initial intake facilities and hand out flyers about the programme, including participation instructions. Additionally, NAT counsellors will be present in the facilities on a regular basis. With it, refugees who would like to participate can request to register for participation. Moreover, with bi-monthly visits at the initial intake facilities, public health experts and research assistants will invite refugees to participate in the online self-assessments of the Well-being Monitor.

## Assignment of interventions: allocation

Random allocation to treatment and control conditions is crucial in establishing causal inference. However, this approach is costly and raises ethical concerns when evidence-based treatment is existing and vulnerable populations are studied over extended periods. Therefore, the regression discontinuity design (RDD), introduced by Thistlethwaite and Campbell in the 1960s [141], serves as a powerful quasi-experimental alternative and has been applied in the field of counselling [142]. In brief, the RDD defines eligibility based on a *bandwidth* around a cutoff of a continuous variable that determines assignment. The premise underlying RDD is that participants near the cutoff are similar in all relevant respects except for treatment assignment, thus “as-if random” in this localized context. The *fuzzy* RDD also allows for deviation from the cutoff as criteria for single cases (systematic manipulation is however not allowed). With it, RDD provides an unbiased estimate of the local treatment effect, simulating a randomized controlled experiment for participants near the cutoff or within the bandwidth, respectively [141, 143–146].

### Sequence generation

Not applicable.

### Concealment mechanism

Not applicable.

### Implementation

To assign participants according to the RDD principles, we will use the RHS-15 (items 1–13) as eligibility criteria with two critical thresholds at 13 and 36 (see Fig. 4) as foreseen in the stepped-care model of the *NAT counselling intervention*. The RDD then assumes that the allocation to the conditions is nearly random within the determined bandwidth (RHS sum scores just above or below the cutoffs) and potential factors that would manipulate treatment effect vary randomly across participants in both groups. The *fuzzy* versus the *sharp* design version takes into account real-world implementation settings recognizing that participants with RHS scores in the yellow range need to be assigned to the red group, for instance, in cases of suicidal ideation or other negative psychological developments that requires treatment by clinical psychologist.

**Fig. 4 Fig4:**
[figure not shown]
Hypothetical values of the NAT counselling intervention regression discontinuity design. RHS = Refugee Health Screen

## Assignment of interventions: blinding

### Who will be blinded

Neither participants nor assessors will be actively blinded.

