All steps of the NAT counselling intervention are carried out by trained counsellors under the supervision of NET experts (from vivo international e.V. and the University of Konstanz) or otherwise trained licensed psychotherapists. The NAT counsellors themselves are peers in terms of their cultural and migrant background and therefore have similar biographical experiences, moreover are familiar with and well-integrated into German culture and have good language skills (mother tongue and German) and strong social skills. It is recognised that conditions in the countries of origin vary and therefore the requirements for recruitment and inclusion of counsellors in the project programme have not been rigidly defined but are rather based on the real-world setting. However, high motivation, impartiality and strong integrative and social skills are prerequisites for participation in the NAT training programme. Exclusion criteria for counsellors include: suffering from a mental illness, holding extreme or radical religious or ideological views, have insufficient language skills or illiteracy in German. In addition, we provide a screening for PTSD symptoms in an initial session using the PTSD Checklist for DSM-5 [127, 128]. Following this assessment, participants are provided with an individualised information session on the potential psychological impact of the project and supported to make their own decision as to whether or not they are ready to train and work as a counsellor and to undergo counselling themselves. Due to the sensitive nature of this personal health information, no written records are made or kept.

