### Outcomes

Outcomes of interest include the participants´ somatic and psychological symptoms, social integration, mental health literacy of the client, general life satisfaction, and post-migration stressors. Baseline and a follow-up assessment will be administered by NAT counsellors in face-to-face interviews and will assess psychological symptoms and social integration. Additional instruments are listed in Table 3 will be administered online.

**Table 3 Tab3:** List of instruments of the well-being monitor

Outcome	Measure	Author	Admin.
Somatic symptoms	Somatic Symptom Scale-8 (SSS8)	Gierk et al. [129]	online
Psychological symptoms	Refugee Health Screener (RHS-15)	Hollifield et al. [130]	both
Life satisfaction	Satisfaction with Life Scale (SWLS)	Diener et al. [131]	online
Social networks	Lubben Social Network Scale (LSNS-6)	Lubben [132]	online
Social and economic integration	Immigration Policy Lab Integration Index (IPL-12)	Harder et al. [133]	both
Mental Health literacy Scale	Mental Health Literacy Scale (MHLS)	O’Connor et al. [134]	online
Resilience	Brief Resilience Scale (BRS)	Smith et al. [135]	online
Self-efficacy	General Self-Efficacy Short Scale-3 (GSE-3)	Doll et al. [136]	online
Food insecurity	Food Insecurity Experience Scale (FIES)	Cafiero et al. [137]	online
Food environment	Access to preferred food types	Adapted from Hadley et al. [138]	online
Aggression	Adapted version of the event scale of the appetitive aggression scale	Weierstall et al. [139]	both
Note: Both = to face-to-face interviews and online			

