#### Assessment (refugees)

Data collection from refugees begins with a face-to-face interview conducted by one of the NAT counsellors (see Sect. Intervention description) and continues with 10-minute monthly online assessments (Well-being Monitor). Approximately 6 to 9 months after the initial screening, refugees will be invited to a face-to-face follow-up interview.

At the start of the face-to-face baseline interview, we will ask for demographic information, screen for trauma related symptoms, and collect information on social and economic integration. The follow-up interview after 6–9 months will re-assess levels of psychological distress and integration.

The 15-item Refugee Health Screener [123] will be used to assess the severity of trauma related reactions. The RHS was adapted from validated instruments for depression, anxiety and PTSD to screen for trauma related reactions in refugee populations. Each item is rated on a scale from 0 (not applicable at all) to 4 (extremely) and a total score of items 1–13 indicates the severity of symptoms (0–52) and the intensity of treatment required. Items ask for instance for nightmares, loss of interest or other trauma related symptoms. Items 14 and 15 are taken into account in a qualitative way. The RHS was recently validated with refugees in the German context [124]. Kaltenbach et al. [124] found high sensitivity and good feasibility, reliability and validity for both the self-rating and interview versions. Strong psychometric properties of the RHS were also found in other studies in Germany [147, 148] and elsewhere [149, 150].

An adapted version of the Appetitive Aggression Scale [139] for refugees will be used to assess aggression. The AAS is a 15 item semi structured interview that measures appetitive aggression according to the extent of agreement to statements, on a scale ranging from 0 (disagree) to 4 (agree) for each item. A total sum score will be used to measure severity of aggression (max 60).

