### Plans to promote participant retention and complete follow-up

NAT counsellors will organise face-to-face follow-up sessions to ensure a personalised and supportive environment for participants. To increase engagement with the online assessment, public health experts and research assistants will be on site to support clients. In the event of a participant dropping out or deviating from the intervention, efforts will be made to collect relevant outcome data, allowing for a comprehensive analysis of the factors influencing participation outcomes, while respecting the participants’ right to withdraw from the study. In addition, participants will receive vouchers or cash as a monetary incentive (5€) for completing the online surveys, providing a motivational incentive for continued participation and completion of follow-up assessments. These retention strategies are designed to ensure data integrity and maximise the depth of insight gained from the study.

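### Unblinded NAT counsellors, from the pool that delivers NAT, take the follow-up RHS and the baseline RHS that allocates; nothing keeps treater and interviewer apart, and no named check would show the resulting bias.

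*Protocol article*

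**What the plan says.** On blinding (Who will be blinded): "Neither participants nor assessors will be actively blinded".

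On who assesses (Outcomes): "Baseline and a follow-up assessment will be administered by NAT counsellors in face-to-face interviews and will assess psychological symptoms and social integration". The section Assessment (refugees) adds that "Data collection from refugees begins with a face-to-face interview conducted by one of the NAT counsellors", and the retention section that "NAT counsellors will organise face-to-face follow-up sessions".

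On who treats (Eligibility criteria): "All steps of the NAT counselling intervention are carried out by trained counsellors".

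The abstract names the RHS-15 as primary outcome without giving the mode of administration. The baseline RHS (items 1–13, range 0–52) also allocates: up to 12 is green, 13–36 is yellow and receives NAT, 37 or more is red. On the cutoffs, the allocation section says that "systematic manipulation is however not allowed".

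A self-rated RHS exists alongside. Table 3 lists the RHS-15 as given both in person and online. All participants are invited to the online monitor under a separate consent, and research staff invite and support them. The article reports "high sensitivity and good feasibility, reliability and validity for both the self-rating and interview versions".

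**The concern.** Participants and counsellors cannot be blinded to NAT. Who takes the follow-up interview, however, can be chosen. After narrative sessions about a client's life and traumas, the same counsellor may later ask that client, face to face, how severe the symptoms are. Red, green and still-waiting clients have received no NAT from anyone in the pool, so they have no such relationship with their interviewer. A downward shift of follow-up scores on the NAT side cannot be told apart from a treatment effect.

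The baseline score is exposed as well. An interviewer who knows the cutoffs takes the score on which one point separates NAT from referral (36/37) or from watchful waiting (12/13). If scores were nudged, clients on the two sides would no longer be comparable, and the causal claim rests on that comparability.

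**Working it through.** The document gives no figure for rating bias, no RHS standard deviation and no target sample size in its text, so there is no figure of the plan to reproduce. The check has three parts.

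**1. Would the planned checks show the problem?** Statistical methods for primary and secondary outcomes names the following:
- Outcome scatterplot and jumps in covariates at the cutoff: covariates are unaffected by how the follow-up RHS is taken.
- Choice of bandwidth: a shift across the whole NAT side persists at every bandwidth.
- Placebo tests on exogenous covariates: unaffected, as above.
- Placebo cutoffs: a shift that starts at the true cutoff gives no jump elsewhere.
- Unspecified falsification tests: no content is given.

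None of the named checks detects interviewer bias at follow-up. None looks at the number of clients at each baseline score. Covariate tests would show sorting only if a measured covariate carried the difference. The Limitations section does not mention interviewer bias.

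**2. Follow-up bias, illustration.** The effect is the gap between two regression lines at the cutoff, so a shift of b points on one side adds b to it. In a simple two-group comparison with no true effect, SE = SD × √(2/n) and P(significant) = 1 − Φ(1.96 − b/SE) + Φ(−1.96 − b/SE). Here b is the shift in excess of any shift in the control group. SD, n and b are assumptions. With SD 8 and n = 100 per group, SE = 8 × √0.02 = 1.13:

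| b (RHS points) | P(significant) |
|---|---|
| 0 | 0.05 |
| 1 | 0.14 |
| 2 | 0.42 |
| 3 | 0.76 |

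For b = 2, with SD 6–10 and n 50–200 per group, the range is 0.17–0.92. This is not the regression discontinuity test itself; it shows only that small shifts matter.

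**3. Baseline sorting at 36/37, illustration.** The assumptions are six integer scores on each side (31–36 and 37–42), equal counts, a flat trend and no treatment effect. A share p of clients who would score 37 is recorded as 36, and these clients have a follow-up RHS 5 points lower than those left at 37. Set the mean of all who would score 37 to zero.
- Those left at 37: mean 5p, weight 1 − p.
- Those moved: mean −5(1 − p). Score 36 then has mean −5p(1 − p)/(1 + p) and weight 1 + p.
- A weighted straight line is fitted on each side and read at 36.5.

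| p | Mean at 36 | Mean at 37 | Left line at 36.5 | Right line at 36.5 | False jump |
|---|---|---|---|---|---|
| 0.1 | −0.41 | 0.50 | −0.26 | 0.28 | 0.54 |
| 0.2 | −0.67 | 1.00 | −0.43 | 0.53 | 0.96 |
| 0.3 | −0.81 | 1.50 | −0.54 | 0.74 | 1.28 |

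The jump favours NAT because those moved were assumed to do better. If the 5 points were measured against all who would score 37, including those moved, the jumps would be 0.60, 1.20 and 1.83. At p = 0.3 that implies a gap of 5/0.7 = 7.1 points from those left behind, so the smaller figures are the ones to use.

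**The case against.** The strongest defence is that this is an openly declared choice in a naturalistic study, with no contradiction or wrong figure behind it. Several of its arguments stand.

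- **The treating counsellor is not said to be the interviewer.** The article speaks only of one of the counsellors. A reader might infer that counsellors assess their own clients; the text leaves that possible but does not state it.
- **The bias is not confined to NAT clients.** Counsellors also interview red and green clients, so courtesy can act in every group. Only the difference between groups biases the contrast.
- **Counsellors do not rate in the strict sense.** The RHS records the client's own answers, so the main route is influence on those answers.
- **Sorting is forbidden, and nothing shows that it will occur.** Clients in the yellow range may be moved openly to red on clinical grounds, so a clinical concern needs no change of score. The article does not say that counsellors see a running total. A named density test or a survey setting is a detail that an article may leave to fuller documents.
- **Making the self-rated RHS primary is a trade-off.** It needs separate consent, and response may differ between groups. A self-rated follow-up set against an interview baseline would mix mode with change in the mixed models, the reliable change index and hypotheses 2a, 2b and 3. It is also still unblinded self-report. The documents do not support replacing the primary mode.
- **A second language-matched counsellor may not be available at each site.** The article does not say.

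What these arguments leave untouched is that no rule separates treater from interviewer, and that the named checks cannot see the consequence.

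**Conclusion.** The point holds as a weakness that should be fixed. The article fixes unblinded assessors, face-to-face RHS interviews by NAT counsellors at baseline and follow-up, and delivery of NAT by the same pool. From these it follows that interviewer influence can differ between groups, mainly on the NAT side, and that it would appear in the estimate as benefit.

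The size is unknown. The 0.5–1.3 points for sorting rest on the assumed share moved, the assumed 5-point advantage and its direction. The probabilities for follow-up bias rest on assumed SD, group size and shift. None of these is an estimate of bias in this study, and a reader should not infer that a result in favour of NAT would be an artefact.

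**What to change.** 1. State that the follow-up RHS interview is taken by an existing NAT counsellor who did not treat that client, where language match allows, and record who interviewed whom.
2. State that the interview RHS is the primary mode, so that it matches baseline. Prespecify the self-rated RHS nearest to 6–9 months as a sensitivity analysis in all groups, noting that it is still unblinded and depends on separate consent and on response.
3. Add a check of the baseline score distribution at 12/13 and 36/37 to the design's validity tests. As a precaution, have the survey software lock all items before the score is shown.
4. List interviewer bias among the limitations.

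The cost is protocol wording, a survey setting, one added sensitivity analysis, and some scheduling work where few language-matched counsellors are available. No sample-size figure changes.

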### Procedure for unblinding if needed

Not applicable.

## Data collection and management

### Plans for assessment and collection of outcomes

Data will be collected from the participating refugees and from the counsellors who deliver the treatment.

#### Assessment (refugees)

Data collection from refugees begins with a face-to-face interview conducted by one of the NAT counsellors (see Sect. Intervention description) and continues with 10-minute monthly online assessments (Well-being Monitor). Approximately 6 to 9 months after the initial screening, refugees will be invited to a face-to-face follow-up interview.

At the start of the face-to-face baseline interview, we will ask for demographic information, screen for trauma related symptoms, and collect information on social and economic integration. The follow-up interview after 6–9 months will re-assess levels of psychological distress and integration.

The 15-item Refugee Health Screener [123] will be used to assess the severity of trauma related reactions. The RHS was adapted from validated instruments for depression, anxiety and PTSD to screen for trauma related reactions in refugee populations. Each item is rated on a scale from 0 (not applicable at all) to 4 (extremely) and a total score of items 1–13 indicates the severity of symptoms (0–52) and the intensity of treatment required. Items ask for instance for nightmares, loss of interest or other trauma related symptoms. Items 14 and 15 are taken into account in a qualitative way. The RHS was recently validated with refugees in the German context [124]. Kaltenbach et al. [124] found high sensitivity and good feasibility, reliability and validity for both the self-rating and interview versions. Strong psychometric properties of the RHS were also found in other studies in Germany [147, 148] and elsewhere [149, 150].

An adapted version of the Appetitive Aggression Scale [139] for refugees will be used to assess aggression. The AAS is a 15 item semi structured interview that measures appetitive aggression according to the extent of agreement to statements, on a scale ranging from 0 (disagree) to 4 (agree) for each item. A total sum score will be used to measure severity of aggression (max 60).

Integration will be assessed using the short version of the Immigration Policy Lab Integration Index (IPL-12) [133]. The underlying concept is to identify and assess integration as both the knowledge and ability to thrive in the host society, rather than as mere assimilation. The index measures six dimensions of integration, namely psychological, economic, political, social, linguistic, and navigational integration. Various studies found a high construct validity and is broadly applicable to different refugee populations [151].

The 5-item Satisfaction with Life Scale (SWLS) [131]; is a widely used self-report questionnaire designed to measure an individuals’ subjective well-being and overall satisfaction with life. Participants are asked to rate each statement on a scale from 1 (strongly disagree) to 7 (strongly agree). The items of the SWLS items cover the following domains: *Standard of living*: The extent to which individuals feel that their standard of living meets their expectations and needs. *Life in general*: Overall assessment of life, including both positive and negative aspects. *Achievements in Life*: Perceptions of personal achievements, accomplishments, and success. *Relationships*: Satisfaction with social relationships, including family, friends, and community. The total score, obtained by summing the ratings for each item, provides a quantitative measure of an individual’s life satisfaction. Higher scores indicate greater life satisfaction, while lower scores indicate lower satisfaction. The SWLS is a concise and reliable tool for assessing subjective well-being and has been widely used in psychological research and clinical settings [131, 152–156].

The 8-item self-report Somatic Symptom Scale-8 (SSS8) [129]; will be used to assess the severity of somatic symptoms, asking whether the client suffered from fever, cough, diarrhoea, headache and other somatic symptoms in the last 14 days. A total score is calculated to indicate symptom burden, with scores ranging from 0 to 27, with higher scores indicating greater symptom burden. The high reliability and validity of the instrument has been demonstrated in large samples not only in Germany [157–159] but also elsewhere, including in self-administered online surveys [160–162].

Social integration will be assessed with an adapted 9-item version of the Lubben Social Network Scale (LSNS-9) [132, 163]; asking for kin and non-kin related ties as well as social networks with individuals born in Germany. The LSNS is particularly advantageous as it has been validated across various cultural contexts and has shown strong correlations with important health outcomes, including depression, mortality, and overall physical health, making it a robust tool for assessing social engagement among refugee populations [132, 163, 164].

Mental health literacy refers to the individuals’ ability to access and utilise mental health services effectively, and to recognize symptoms of mental health disorders. This facilitates prevention, early intervention, self-help, and implementation of evidence-based mental health care. We will use the Mental Health Literacy Scale (MHLS) [165]; to measure refugees’ knowledge and beliefs related mental health issues, focusing ontwo of its five domains: i) knowledge of mental health information sources and services (measured by items 16–19), assessing confidence in finding mental health information and accessing healthcare resources. And ii) beliefs and attitudes toward mental illness (measured byitems 20–28), assessing stigmatising attitudes and beliefs about mental illness, such as whether it’s a sign of weakness, if people with mental illness are dangerous, and willingness to seek professional help. Using this scale will allows us to assess refugees’ understanding of mental health issues and their attitudes toward seeking help, which can have a significant impact on the effectiveness of such intervention programme. This instrument has been applied in numerous studies with refugees demonstrating that individuals with higher levels of health literacy exhibit higher levels of health-seeking behaviours [166–168].

The Brief Resilience Scale (BRS) [135]; is a psychological instrument designed to measure an individual’s ability to withstand or recover from difficult circumstances in life. The scale consists of six items, and respondents rate their agreement with statements about resilience on a scale ranging from 1 (strongly disagree) to 5 (strongly agree). The BRS is a brief and widely used tool for assessing an individual’s capacity for resilience in the face of adversity. It focuses on aspects such as adaptability and the ability to maintain a positive outlook during difficult times [169–172].

The Food Insecurity Experience Scale (FIES) [138]; is a survey-based experiential measure. It is a globally used and validated measure of experiences and behaviours related to difficulties in accessing food [173]. Eight items ask about worrying about food scarcity, eating less nutritious food, eating fewer kinds of food, skipping meals, eating fewer types of food, running out of food, being hungry and going without food for a whole day. Each item refers to a 4-week recall period and can be answered with yes [1]/no [0]. The scale is validated using a scoring algorithm based on a Rasch model. Equating categorises respondents as food secure, mildly FI, moderately FI or severely FI [174]. Moreover, we will use different items to measure customization within the new food environment; indicating autonomy to practice preferred eating habits and thus, live one’s identity including cultural heritage. Previous studies have demonstrated higher levels of customization associated with integration and settlement [175, 176], as well as overall wellbeing through the increased capacity for self-agency and self-sufficiency [177].

